In high resource settings, there is the option for mid-trimester risk prediction using transvaginal ultrasound measurement of cervical length measurement and cervico-vaginal fetal fibronectin [14–18] for identification and care of women who are already deemed to be at risk due to clinical history (previous PTB, previous mid-trimester miscarriage or premature rupture of membranes). These tests for predicting PTB risk are invasive, expensive, require skilled workforce and facilities and are not feasible for rural Indian setting where such facilities are largely unavailable or scarce. Development of an acceptable, non-invasive, ‘point of care’ test for accurate prediction of women at risk of early PTB has considerable potential to reduce infant deaths in low-resource settings through improvements in antenatal and postnatal care uptake and or by referral of high risk women to higher level health facilities with experience in care of vulnerable infants. A small study in the UK has indicated that salivary progesterone concentrations are significantly lower from 24 weeks of pregnancy in women, who had a spontaneous PTB (< 34 weeks gestation) [19]. This highlighted the potential of using salivary progesterone measurements for the prediction of early preterm labour and determining specific women that might benefit from intervention [12, 20–25]. Subsequently, two further studies have confirmed the predictive potential of salivary progesterone measurements in urban populations in India (high risk women) [26] and Egypt [27] (high risk and low risk women). Both indicated that salivary progesterone can identify women destined to deliver < 34 weeks with a sensitivity, specificity, positive and negative prediction values of 83–84%; 86–90%, 60–89.8% and 85.9–95% respectively. With this backdrop, our study aim is to assess and validate the use of a non-invasive salivary progesterone test in a community setting where there is limited or no routine intervention for PTB, to obtain definitive evidence to support the widespread introduction of salivary progesterone testing for PTB in India.

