### Study objectives

To determine the association and assess the performance of a salivary progesterone test (specificity, sensitivity, predictive value and ROC) for prediction of PTB risk at < 34 weeks and < 37 weeks of gestation.To assess the feasibility, and acceptability to women and health care workers, of this test in a rural setting.

As part of objective two, the goal is to gain a fuller understanding of the range of facilitating factors and barriers influencing the use of salivary progesterone PTB tests in Indian rural settings.

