### Study outcomes

Three major outcomes will be determined.

i. The association between salivary progesterone at 24–28 weeks of pregnancy and PTB.

ii. Performance of salivary progesterone test (sensitivity, specificity, predictive values and ROC areas) will be produced for different cut-off values of salivary progesterone for prediction of PTB (< 34 and < 37 weeks of gestation).

iii. Evidence of feasibility and acceptability of this low cost innovation for early identification of pregnant women in rural low resource setting.

For preterm birth, the primary endpoint will be spontaneous preterm birth or PPROM < 34 weeks and secondary endpoints < 37 weeks of pregnancy, < 30 weeks. Additional secondary endpoints will include gestation at delivery and a range of maternal and neonatal outcomes (composite and individual.

A qualitative approach will be used to determine the acceptability of the salivary progesterone test to pregnant women and frontline functionaries (qualitative interviews).

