### Sample size and data analysis

A significant difference between cases of PTB and controls is not sufficient to show that a test is clinically useful. Both sensitivity and specificity must be evaluated. Accurately determining the sensitivity is harder (due to smaller numbers), and the sample size determination accordingly concentrates on this. Based on the PTB rates in two study districts (~ 23%), recruitment of 2000 women would potentially identify 460 preterm deliveries at < 37 weeks’ providing ample power to predict PTB at this gestation and to use data for discovery and validation. Data from Lachelin et al., [19] indicates the salivary progesterone test works best to detect birth < 34 weeks, but this incidence for this gestation is not known for the study districts. However, if 189 cases of PTB < 34 weeks’ are identified (9.5% incidence), this would provide 90% power to distinguish 80% from 70% sensitivity. Calculations were carried out in Stata version 13.1 using the command ‘sampsi’ (StataCorp, College Station, Texas).

At study completion, data will be downloaded into a statistical package in the statistical package Stata, version 15 or later, (StataCorp) and additional data cleaning checks applied. Clinical and pregnancy outcome data will be described for the whole cohort.

Additional predefined exclusion criteria relating to sample availability and contamination, and pregnancy outcome (e.g. iatrogenic PTB, maternal medications such as antidepressants and progesterone, use of cervical cerclage or Arabin pessary).

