The data will be randomly split into training and validation sets, each containing the same number of cases (premature deliveries before 37 and 34 weeks) and controls (term deliveries). The training set will be used to determine the best cut-offs to use for a rule-in and a rule-out test. Based on Priya et al., [26], a limited number of simple cut-offs will be investigated: 500, 1000, 1500, 2000, 2500, 3000 pg/ml. These results will define two thresholds, allowing women to be triaged into three groups: “green” (salivary progesterone above the upper threshold), “amber” (progesterone between the two thresholds) and “red” (progesterone below the lower threshold). It is envisaged that if the test proves suitable for general use, the “green” group will receive usual care; the “amber” group will receive more intense advice about meaning of dating scan, due date, etc.; and the “red” group will be advised to change their birthing plan to include delivery in a district tertiary healthcare centre with a neonatal intensive care facility. Following STARD guidelines [32] for diagnostic tests, measures of test performance (sensitivity, specificity, predictive values and ROC areas) will be produced with 95% confidence intervals for the two cut-offs selected as predictors of the primary endpoint: PTB < 34 weeks of gestation, the secondary endpoints: PTB < 37 weeks’ and < 30 weeks’, and other important outcomes: perinatal and maternal and neonatal death and associated morbidities.

Qualitative data will be analysed following COREQ [33] standards. All the qualitative data collected through in-depth interviews will be translated into English transcripts. The analysis of the transcripts will be done using inductive approach. Themes will be identified during the review of the transcripts manually and further these themes will be grouped into key categories.

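### The ROC area is specified for the two selected cut-offs, not for continuous progesterone, and so would understate the assay's discrimination if its ROC curve is concave

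*Protocol article*

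**What the plan says.** All references are to the protocol article; no separate statistical analysis plan was available.

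- **Study objectives** name the measure without defining it: "performance of a salivary progesterone test (specificity, sensitivity, predictive value and ROC) for prediction of PTB risk".
- **Study outcomes**: "Performance of salivary progesterone test (sensitivity, specificity, predictive values and ROC areas) will be produced for different cut-off values" of salivary progesterone.
- **Sample size and data analysis** lists the candidate thresholds: "a limited number of simple cut-offs will be investigated: 500, 1000, 1500, 2000, 2500, 3000 pg/ml". It continues: "These results will define two thresholds, allowing women to be triaged into three groups". Of the final reporting it says: "measures of test performance (sensitivity, specificity, predictive values and ROC areas) will be produced with 95% confidence intervals for the two cut-offs selected".

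The analysis section applies that last sentence to delivery before 34, 37 and 30 weeks and to other outcomes. No section describes an area computed from the undichotomised concentration.

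**The concern.** An ELISA concentration in pg/ml has one ROC curve and one area per endpoint. That area is the probability that a randomly chosen case has a lower concentration than a randomly chosen control, and it does not depend on a threshold. Once the concentration is cut at a threshold, the ROC curve has a single interior point, and its area is the average of sensitivity and specificity. Such a figure is redundant, and it takes one value at the rule-in threshold and another at the rule-out threshold although the assay is the same.

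ROC is a named performance measure in the objectives, and the Background says the study seeks definitive evidence to support wide introduction of the test. Readers will compare its ROC area with those of other predictors. A value that is low because of dichotomisation would make that comparison misleading.

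**Working it through.** **The plan's own figures.** The article states no ROC area, so there is none to reproduce. The one design figure nearby is: "if 189 cases of PTB < 34 weeks’ are identified (9.5% incidence), this would provide 90% power to distinguish 80% from 70% sensitivity". A one-sample normal-approximation test (null 0.80, alternative 0.70, two-sided 5% assumed) gives n = [1.960·√(0.8·0.2) + 1.282·√(0.7·0.3)]² / 0.10² = (0.784 + 0.587)² / 0.01 = 188.04, rounded up to 189, with 90.1% power. It reproduces, and the present point does not depend on it.

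**Inputs.** The Background reports, for delivery before 34 weeks, "sensitivity, specificity, positive and negative prediction values of 83–84%; 86–90%, 60–89.8% and 85.9–95% respectively". Only the sensitivity (Se) and specificity (Sp) ranges are used.

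**Step 1: area of a dichotomised test.** A case–control pair is ranked correctly with probability Se·Sp and tied with probability Se(1−Sp) + (1−Se)Sp. Counting ties as one half:

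area = Se·Sp + ½[Se(1−Sp) + (1−Se)Sp] = (Se + Sp)/2.

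This is exact. A simulation gave 0.7263 on both sides.

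**Step 2: area of the continuous marker through the same point.** This assumes an equal-variance binormal model: d = z(Se) + z(Sp), area = Φ(d/√2).

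| Se | Sp | d | Single cut-off, (Se+Sp)/2 | Continuous, Φ(d/√2) | Gap |
|---|---|---|---|---|---|
| 0.83 | 0.86 | 0.954 + 1.080 = 2.034 | 0.845 | 0.925 | 0.080 |
| 0.84 | 0.86 | 0.994 + 1.080 = 2.075 | 0.850 | 0.929 | 0.079 |
| 0.83 | 0.90 | 0.954 + 1.282 = 2.236 | 0.865 | 0.943 | 0.078 |
| 0.84 | 0.90 | 0.994 + 1.282 = 2.276 | 0.870 | 0.946 | 0.076 |

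**Step 3: rule-in and rule-out thresholds.** The article does not say what accuracy the two thresholds should reach, so this step assumes 95% specificity for rule-in and 90% sensitivity for rule-out. With d = √2·z(true area):

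- rule-in sensitivity = Φ(z(0.05) + d);
- rule-out false-positive rate = Φ(z(0.90) − d).

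For the three-category reading (both thresholds in one ordinal test), the area is the trapezoid through (0, 0), the rule-in point, the rule-out point and (1, 1).

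| True continuous area | d | Rule-in Se | Rule-in area | Rule-out false-positive rate | Rule-out area | Three-category area |
|---|---|---|---|---|---|---|
| 0.75 | 0.954 | 0.245 | (0.245+0.95)/2 = 0.597 | 0.628 | (0.90+0.372)/2 = 0.636 | 0.690 |
| 0.85 | 1.466 | 0.429 | (0.429+0.95)/2 = 0.689 | 0.427 | (0.90+0.573)/2 = 0.737 | 0.806 |

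Example of the trapezoid for 0.85: 0.05·0.429/2 + (0.427−0.05)·(0.429+0.90)/2 + (1−0.427)·(0.90+1)/2 = 0.011 + 0.251 + 0.544 = 0.806.

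The three-category gaps are 0.75 − 0.690 = 0.060 and 0.85 − 0.806 = 0.044. Separate areas for the two thresholds would differ from each other by 0.636 − 0.597 = 0.039 and 0.737 − 0.689 = 0.048, for one and the same assay.

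**The case against.** The strongest reply is that the parenthesis is a stock list of accuracy measures followed by one trailing clause, and that the authors probably meant an ordinary ROC area. Part of this stands. The Study outcomes wording about different cut-off values also describes how any ROC curve is built, and the bare ROC in the objectives carries no cut-off. The plural can be explained by the several endpoints. Nothing says outright that progesterone is dichotomised before the area is computed. The analysis section, however, attaches the areas and their confidence intervals to the two selected cut-offs, and no section provides the other quantity. This is a stated rule that points to the wrong figure, rather than a detail left for later.

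A second reply is that the two thresholds define one three-group test. On that reading (Se+Sp)/2 does not apply, there is one area per endpoint, and the gap is smaller. That is fair. The area is still too low for the assay, by about 0.04–0.06 in the cases worked.

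A third reply is that the area of a thresholded test is a valid summary of that test. It is; it misleads only when read as the discrimination of the assay. That is how a ROC area is normally read.

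A reader might also infer that the plan confines the ROC area to the validation half and so estimates it on half the cases. The text does not support that as fact. The training set is used to choose the cut-offs, but the reporting sentence names no data set. Use of the validation half is a reasonable inference, no more.

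**Conclusion.** The point stands as a flaw in what is specified, of modest weight. Followed literally, the analysis section yields either a redundant, threshold-dependent area for each cut-off or a three-category area. Both understate the assay's discrimination. The direction requires only that the continuous ROC curve be concave. The size rests on the equal-variance binormal assumption: about 0.08 for a single cut-off at the accuracy quoted in the Background, more at extreme rule-in or rule-out thresholds, and about 0.04–0.06 for the three-category reading under the assumed thresholds.

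It would be tempting to conclude that the study's main accuracy results are compromised. They are not. Sensitivity, specificity and predictive values are reported separately with confidence intervals, the sample size is built on sensitivity, and no cut-off choice or success criterion is stated in terms of the ROC area. Any claim about lost precision is conditional, because the data set for the ROC area is not stated.

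**What to change.** Replace the single list in Sample size and data analysis with two statements:

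1. The ROC area, with its 95% confidence interval, will be estimated from salivary progesterone as a continuous measurement, separately for delivery before 34, 37 and 30 weeks.
2. Sensitivity, specificity and predictive values, with 95% confidence intervals, will be reported at the two selected cut-offs.

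Align the Study outcomes wording with this, and state which data set each measure uses. The continuous area involves no cut-off selection, so it can use all evaluable women. If the present intention is to use only the validation half, this would also improve precision; if not, there is no such gain.

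The cost is a sentence or two of text and a standard Stata command. No additional data are needed, and the sample size, the cut-off selection and the other performance measures do not change.

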## Discussion

The protocol described includes adaptations that were implemented early in the study to address the operational challenge of ensuring timely USG. Initially, it was planned to only include women who had a USG dating pregnancy scan performed by 13^+ 6^ weeks of gestation. However, it was clear that the reported self-reported LMP, which was used to inform recruitment, and USG schedules were very unreliable mainly because of the social taboo associated with pregnancy disclosure in the first and second trimester. Following discussion, review of the literature and inclusion of additional USG measurement parameters [31], the window for USG dating was increased, with a focus on ensuring women were scanned by 16 weeks’ for the saliva testing if possible. This was decided to be a pragmatic approach for the study setting, and indeed, if the test proves to work, the revised research criteria would better reflect real-life conditions for implementation.

In India, the Maternal, Newborn, Child and Adolescent Health (RMNCH+A) strategic framework of 2013 laid out a vision and a plan for the country to end preventable newborn deaths, accelerate progress, and scale up high-impact yet cost-effective interventions. The successful validation of a cost effective, simple to use tool, with a predictor value of 70–80% for PTB, will allow easy identification of pregnant women who are at risk of PTB, who can be directed effectively to an appropriate level of care. Moreover, the Government of India has pledged to improve its neonatal mortality with a strong political will to achieve it. The India Newborn Action Plan (INAP) [34] is India’s committed response to the Global Every Newborn Action Plan (ENAP), launched in June 2014 at the 67th World Health Assembly, and Reproductive, One of the specific goals of INAP is ‘Ending Preventable Newborn Deaths to achieve “Single Digit NMR” by 2030, with all the states to individually achieve this target by 2035’. Although, the intervention package ‘Antenatal Screening for high risk pregnancies/complications and their management’ has shown considerable impact [35] on the prevention of many of the newborn deaths, stillbirths, and maternal deaths, it does not include early diagnosis/screening of PTB, which is the major cause of newborn deaths in India. The salivary progesterone test, if successful, will fill in the gap of providing a simple diagnostic tool for predicting PTB which can be easily adopted within the routine pregnancy/antenatal period at the level of community health workers and equip health system with an appropriate management plan for at-risk women for the rural settings. However, in tandem, it will require adequate USG facilities in these areas and increased education of women so that they reveal pregnancy earlier and access USG for accurate pregnancy dating. The future scale-up of the test, if successfully combined with accurate pregnancy dating, could lead significant improvements in care for pregnant women and neonatal outcomes related to PTB.

## Abbreviations

ANC: Antenatal care
ASHA: Accredited Social Health Activist
MAMTA-HIMC: Mamta Health Institute for Medical Sciences
MGIMS: Mahatma Gandhi Institute for Medical Sciences
NNMR: Neo natal mortality rate
ORW: Outreach Worker
PTB: Preterm Birth
USG: Ultra sonography
